## Abstract

**Background:**

Status Epilepticus (SE) is a common neurological emergency associated with a high rate of functional decline and mortality. Large randomized trials have addressed the early phases of treatment for convulsive SE. However, evidence regarding third-line anesthetic treatment and the treatment of nonconvulsive status epilepticus (NCSE) is scarce. One trial addressing management of refractory SE with deep general anesthesia was terminated early due to insufficient recruitment. Multicenter prospective registries, including the Sustained Effort Network for treatment of Status Epilepticus (SENSE), have shed some light on these questions, but many answers are still lacking, such as the influence exerted by distinct EEG patterns in NCSE on the outcome. We therefore initiated a new prospective multicenter observational registry to collect clinical and EEG data that combined may further help in clinical decision-making and defining SE.

**Methods:**

Sustained effort network for treatment of status epilepticus/European Academy of Neurology Registry on refractory Status Epilepticus (SENSE-II/AROUSE) is a prospective, multicenter registry for patients treated for SE. The primary objectives are to document patient and SE characteristics, treatment modalities, EEG, neuroimaging data, and outcome of consecutive adults admitted for SE treatment in each of the participating centers and to identify factors associated with outcome and refractoriness. To reach sufficient statistical power for multivariate analysis, a cohort size of 3000 patients is targeted.

**Discussion:**

The data collected for the registry will provide both valuable EEG data and information about specific treatment steps in different patient groups with SE. Eventually, the data will support clinical decision-making and may further guide the planning of clinical trials. Finally, it could help to redefine NCSE and its management.

**Trial registration:**

NCT number: NCT05839418.

**Supplementary Information:**

The online version contains supplementary material available at 10.1186/s12883-023-03505-y.

## Background

Status epilepticus (SE) is a common neurological emergency defined by the International League Against Epilepsy (ILAE) Task Force on Classification of SE as “ a condition resulting either from the failure of the mechanisms responsible for seizure termination or from the initiation of mechanisms which lead to abnormally prolonged seizures and can have long-term consequences, including neuronal injury or death, and alteration of neuronal networks, depending on the type and duration of seizures” [1]. The duration threshold has been defined for convulsive SE as a seizure lasting longer than 5 min, for focal and/or non-convulsive SE as lasting longer than 10 min or for non-convulsive SE for a total duration of 20% of any 60-minutes period of recording [2, 3].

The current treatment strategies of SE use a tiered approach, in which the sequential administration of different drugs follow pre-defined temporal points. These may not always reflect the severity of the SE episode and need for urgent seizure cessation, hence are rarely strictly adhered to in clinical practice [4–6]. In early SE (5 to 20 min after seizure onset), a parenteral benzodiazepine should be given. In established SE (20 to 40 min) a non-sedating intravenous (IV) anti-seizure medication (ASM) is recommended. Refractory status epilepticus (RSE; 40 to 60 min) is defined as SE persisting despite administration of at least two appropriately selected and dosed parenteral medications, including a benzodiazepine. Super-refractory SE (SRSE) is defined as SE persisting or recurring after 24 h or more of treatment with continuous intravenous anesthetic drugs (CIVADs) [7].

In the last three decades, a few large randomized controlled trials provided evidence for the early stages of SE and established the role of benzodiazepines [8–10]. However, underdosing and/or absence of benzodiazepines as first-line treatment have been widely observed and has been associated with poorer outcome, among others things [11–14].

In 2019, the multicenter randomized double-blind “Established Status Epilepticus Treatment Trial” (ESETT) compared IV fosphenytoin, levetiracetam and valproate for established convulsive status epilepticus (CSE), with similar rates of SE cessation and adverse events, confirmed by recent pediatric studies [15]. Based on these trials, the first and second-line treatments of convulsive SE are well established. Previous studies also suggested that other non-sedative IV ASMs, such as lacosamide or brivaracetam could be effective and safe as second-line treatment or beyond [16–23, 23, 24].

Although CIVADs are recommended as third-line treatment and are safe to use as second-line [25], there is currently limited evidence to guide this third-line and later treatments on convulsive and other types of SE.

In RSE, a randomized trial comparing propofol and barbiturates was initiated in 2006 but was terminated early due to insufficient enrollment. Efficacy was similar between the two drugs but duration of intubation was much longer with barbiturates [26]. Few observational studies compared anesthetic drugs and different doses [27–29]. Overall, data support the choice of midazolam and propofol to treat refractory SE over barbiturates, which are associated with significantly more complications (especially infections) and mortality, but randomized controlled trials are lacking [30–32]. Non-sedating ASMs are an alternative to CIVADs in refractory nonconvulsive cases, but there is a lack of evidence regarding which drug to administer and how, as highlighted by several recent reviews [33] and observational case series [34–36].

There are even fewer data to guide the management of super-refractory SE [37] and for the use of uncommon strategies in this setting, including ketamine, isoflurane [38] the ketogenic diet, electroconvulsive therapy, and neurostimulation [39, 40], hypothermia or immune therapies in SE of suspected autoimmune or autoinflammatory etiology [41, 42].

Further investigation is needed to determine the optimal EEG target in patients with RSE and SRSE. Commonly used EEG surrogates of RSE control include seizure suppression, the emergence of a burst-suppression pattern (BS), or an isoelectric background. Achieving these surrogate endpoints often requires titrating intravenous antiepileptic drugs based on EEG readings. A multinational survey favored BS as the preferred target for CIVAD titration in RSE patients [43], with an interburst interval of around 10 s suggested by experts [44]. Achieving BS could be challenging and was not associated with sustained seizure termination or better outcome in a recent observational study [45]. The adequacy of BS as a surrogate target then lacks substantial evidence [46].

Finally, although the treatment of CSE is well established, these recommendations are often extrapolated to NCSE due to lack of data confirming the appropriateness of this practice. Currently, there is no clear consensus on the treatment of NCSE.

To address all these issues, randomized and controlled trials are needed. Such trials require substantial financial and human resources to achieve sufficient statistical power [47]. This is a challenge for RSE and SRSE, which have a low annual incidence of respectively up to 7 per 100.000 adults and 1 per 100.000 adults [48–50]. Other limitations include the challenges of clinical trials in the emergency setting and in temporarily incapacitated subjects.

Multicenter prospective observational registries offer an alternative approach to randomized controlled trials by collecting data on determinants of outcome, practice variability and allow comparative effectiveness and efficacy studies. Recently, the Sustained Effort Network for treatment of Status Epilepticus (SENSE) has provided real-life data about SE [51–55]. Between January 2011 and June 2015, 1179 episodes of SE in 1049 subjects from eight German-speaking centers in Austria, Germany, and Switzerland, were enrolled in SENSE. Collected data helped provide new insights into the factors contributing to SE cessation and refractoriness, functional outcome, and intubation.

The overarching goal of the Sustained Effort Network for Treatment of Status Epilepticus/European Academy of Neurology Registry on Refractory Status Epilepticus (SENSE-II/AROUSE) is to harmonize the collection of clinical and EEG data from multiple centers on SE to gain further insight on the management of SE across all its semiologies and etiologies, and to compare second- and third-line treatments and beyond. More specifically, we aim to:

identify risk factors of outcome, refractoriness, super-refractoriness.perform comparative effectiveness studies on third-line treatment and beyond, and on the use of cEEG.collect epidemiological data on rare forms and causes of SE.identify key targets for future randomized controlled trials.

## Methods/Design

### Study design

SENSE-II/AROUSE is a prospective, multicenter, observational registry study on consecutive cases of SE in patients 18 years of age or older. We aim to involve university hospitals as well as non-university hospitals to enhance generalizability of our findings.

Currently, 12 high-volume medical centers in Belgium, Austria, Germany, Switzerland, Norway, Finland, and Denmark are involved:

Belgium : Hôpital Universitaire de Bruxelles – Erasme Hospital ([name], [name]) ; Centre Hospitalier Universitaire Brugmann ([name]).Austria: University Hospital Salzburg - Christian Doppler University Hospital ([name], [name]) ; Johannes Kepler University Linz ([name]).Germany: Goethe-Universität Frankfurt am Main ([name], [name]); Klinikum Osnabrück ([name]).United Kingdom: University Hospitals Birmingham ([name]).Switzerland: Universitätsspital Basel ([name], [name]); University Hospital of Geneva ([name]).Norway: Oslo University Hospital ([name]).Finland: HUS Helsinki University Hospital ([name]).Denmark: Odense University Hospital ([name]).

Personnel collecting data from the patient charts and entering data into the database are board certified neurologists, or neurology residents, or medical students in their final year, or study nurses, who will be specifically instructed prior to data collection and personally supervised by one of the principal investigators during the data collection and entry.

Patients will be treated in emergency departments, EEG-laboratories, or intensive care units with electronical data entry and management, or with dedicated data collection sheets in place [56]; thus, type, dosages and time points of drug administration will be easily ascertained. The increasing use of continuous video-EEG (cEEG) monitoring will also allow for exact and reliable determination of cessation of NCSE, and in some cases also of NCSE onset.

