### Clinical data

Variables in Tables 1, 2 and 3 will be collected.

**Table 1 Tab1:** Baseline, SE-related and outcome variables; SE: Status Epilepticus; mRS: modified Rankin Scale; ILAE: International League Against Epilepsy; NCSE: non convulsive status epilepticus; EMSE score: Epidemiology Based Mortality Score in Status Epilepticus

**Demographics and premorbid status**	Age at admission, gender, ethnicity Estimated weight on admission. Location at SE onset Date and time of hospital admission Premorbid Clinical Frailty Scale [60] and premorbid mRS [61]
**Health variables**	History of previous seizures/epilepsy, history of SE Relevant known health problems (comorbidities) as found in Charlson comorbidities index [62]
**SE-related variables** General	Date and time of SE onset Refractory and super-refractory SE Date and time of refractoriness and super refractoriness
Semiology	Semiology according the ILAE [1] Worst seizure type according to STESS score [63] Level of consciousness at SE diagnosis or onset
Etiology	Etiology according to the ILAE and according to the EMSE score SE episode fulfilling criteria of New Onset Refractory Status Epilepticus (NORSE) or Febrile Infection-Related Epilepsy Syndrome (FIRES) [7]
**EEG-related variables**	Date of ictal EEG (if applicable) EEG pattern *(according to the ACNS 2021 terminology and Salzburg criteria for NCSE)* [2, 58, 59] EEG findings as classified in EMSE score [50] If NCSE was diagnosed by EEG and clinical response to IV ASM, then the ASMs and the timing and kind of EEG and clinical improvement are documented. Use of cEEG or repeated EEG in management/diagnosis Used EEG-target for CIVAD : seizure suppression, burst-suppression or flat EEG
**Performed diagnosis procedures**	Brain CT or MRI, continuous video-EEG monitoring (cEEG), fluorine-18 fluorodeoxyglucose (FG) brain positron emission tomography (PET) scan, cerebrospinal fluid analysis, antineuronal antibodies research, brain biopsy, therapeutic drug monitoring, Multimodal Invasive Monitoring or other.
**Outcome-related variables**	Date and time of SE cessation and EEG-documentation of SE cessation Date and time of first-time following commands Date of discharge from hospital mRS at discharge and at 30 days after admission (if still hospitalized) At 90 days after discharge: mRS, recurrence of seizure, ongoing ASM therapy Date and cause of death Reason for withdrawal of life support therapies

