### Management protocol

No common management protocol will be imposed on the participating centers. However, most institutions have established a local protocol that is closely related to the most recent guidelines for the management of SE published by the American Epilepsy Society (AES) in 2016 [64].

In general, diagnosis of SE and related conditions is made based on clinical suspicion using physical examination and, where necessary, EEG (including, cEEG).

In most cases, emergency cerebral imaging with CT or MRI as well as standard emergency blood analysis, and CSF analysis if indicated, will be performed. Most frequently, the first treatment step consists of the administration of a benzodiazepine. If unsuccessful, intravenous administration of ASMs such as levetiracetam, valproate, (fos-)phenytoin, or lacosamide follows. As a third step, another ASM is added or anesthetics such as propofol or midazolam. All treatment decisions will remain at the discretion of the attending physicians.

The use of data acquisition sheets for the very early stages SE (Annex; modified from [56]) and ASM trials for IIC, which are already in place in some centers, will be encouraged to facilitate homogenous and complete data collection.

All participating centers perform cEEG for the following indications:

Management of refractory and super-refractory SE.Suspicion of NCSE after a convulsive SE or seizure (lack of return to neurological baseline).

Some participating perform cEEG for additional indications, such as patients unexplained altered mental status, detection of delayed cerebral ischemia in aneurysmal, subarachnoid hemorrhage.

The availability of cEEG is specific to each center, varying from 7 days a week (including Sundays and holidays) to during working hours on weekdays.

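### Cessation of NCSE cannot be timed exactly where continuous EEG is limited to weekday working hours, and Table 1 lists the ictal EEG by date without a clock time

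*Protocol article*

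**What the plan says.** The Study design section of the protocol article says that the increasing use of cEEG "will also allow for exact and reliable determination of cessation of NCSE", and adds onset for some cases. The sentence is not limited to monitored patients or to particular centres.

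The Management protocol section describes cEEG availability as specific to each centre, "varying from 7 days a week (including Sundays and holidays) to during working hours on weekdays". It gives neither the clock hours nor the number of restricted centres. It lists two indications common to all centres, one of which is "Management of refractory and super-refractory SE".

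Table 1 (Clinical data section) gives the ictal EEG as "Date of ictal EEG (if applicable", with no time. In the same table SE onset is "Date and time of SE onset". Refractoriness, super-refractoriness and SE cessation also carry date and time, and EEG documentation of cessation is listed as an item. Table 2 gives date and time for first-line benzodiazepines, for the first dose of any other ASM, and for the start and stop of CIVADs.

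The Objectives section asks what EEG shows in NCSE and whether it carries clinically relevant information. The aims at the end of the Background include to "perform comparative effectiveness studies on third-line treatment and beyond, and on the use of cEEG".

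**The concern.** Two separate timing problems meet here.

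The first is the end of NCSE. If SE can be recognised only on EEG, its end cannot be observed while no EEG is running. At a centre with restricted hours, the recorded time may then be the time of the next recording rather than the time at which SE stopped. One cessation field cannot show how wide that interval was. Durations would carry an error that differs between centres, in a registry that also asks whether outcome differs between centres.

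The second is the ictal EEG. The registry wants to relate EEG patterns in NCSE to outcome. A pattern recorded before treatment describes the disease. One recorded after a drug may partly describe the drug. With a date but no time, the two cannot be told apart when EEG and drug fall on the same day, so a pattern entered as a predictor may be a consequence of treatment. No later analysis can restore an order that was not recorded.

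**Working it through.** **No stated figure to reproduce.** The article gives no number for cEEG coverage or timing error. What follows illustrates scale under assumed hours.

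**Step 1: coverage of the week.** Let h be the hours of service per weekday (assumed, 8 to 12). Coverage = 5h/168.
- h = 8: 40/168 = 23.8%
- h = 12: 60/168 = 35.7%

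So 76.2% to 64.3% of the week is uncovered.

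**Step 2: length of the gaps.** Weeknight gap = 24 − h, which gives 16 to 12 h. Weekend gap = 72 − h, which gives 64 to 60 h.

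**Step 3: wait from an unobserved end to the next covered time.** Assume that ends are spread evenly over the week, that no recording continues out of hours, that no routine EEG is done and that there is no clinical sign. Each week has four weeknight gaps and one weekend gap. Mean wait for ends outside coverage = (sum of squared gaps / 2) / (sum of gaps).
- h = 8: (4 × 16² + 64²)/2 = 2560, and 2560/128 = 20.0 h
- h = 12: (4 × 12² + 60²)/2 = 2088, and 2088/108 = 19.3 h

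The median solves 4(g − x) + (w − x) = half the uncovered hours, with g the weeknight gap and w the weekend gap.
- h = 8: 128 − 5x = 64, so x = 12.8 h
- h = 12: 108 − 5x = 54, so x = 10.8 h

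The wait exceeds 24 h for (w − 24)/168 of all event times: 40/168 = 23.8% for h = 8 and 36/168 = 21.4% for h = 12.

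**Step 4: which episodes this touches.** The delay applies to NCSE and to other SE visible only on EEG, for example under anaesthetics. It hardly touches convulsive SE whose end is evident at the bedside.

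**Step 5: ordering EEG and drug.** An EEG known only by date can lie anywhere in a 24 h day. If a drug was given t hours into that day, the EEG may fall in the t hours before it or in the 24 − t hours after it, and the clock time of the drug does not help. Order is determined only when the two dates differ, or when timing is recorded elsewhere. Tables 1 and 2 do record timing elsewhere for one subgroup: where NCSE was diagnosed by EEG and clinical response to an intravenous ASM, the timing of the improvement is documented.

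**The case against.** The best reply is that the two sections do not formally contradict each other. One says what cEEG makes possible, the other says where it is available, and nothing states that every NCSE end will be timed exactly. That is fair, and the point is better put as an unqualified claim that fails for some centres. Several further replies also stand:
- Availability is not the same as recording. A cEEG already started may continue overnight, and repeated EEG is listed in Table 1.
- "All participating centers perform cEEG for the following indications", and these include refractory and super-refractory SE, which reduces the dependence on centre without removing it.
- EEG documentation of cessation and the time of first following commands are both collected. The former may separate confirmed from unconfirmed ends. As listed, neither gives the last time at which SE was still seen.
- Table 1 is a variable list in a condensed article, and the data-capture form is not shown. The form may hold a time for the ictal EEG, and the continuous EEG data planned in the Discussion may carry one. The point applies to the table if it is followed as written. Neighbouring items do specify a time, so the omission is worth checking.

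Two stronger readings are tempting and are not supported. A reader might infer that super-refractoriness is misclassified according to weekday. The Study population section defines it by SE persisting or recurring after at least 24 h of CIVADs, not by total SE duration, and CIVAD start and stop times are recorded. A late cessation time in a patient not on CIVADs cannot create it. A reader might also infer that the planned cEEG comparison would make cEEG look harmful. The article names that comparison as an aim and specifies neither its outcome nor its contrast. Outcomes not read from EEG, such as mRS and death, are collected. Either consequence could be stated only conditionally.

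**Conclusion.** The point holds in a limited form. The claim of exact and reliable NCSE cessation cannot be sustained for patients not under cEEG when SE stops, and the article's own account of availability implies that some centres will have such patients. For SE visible only on EEG, the recorded end can be late by an unknown amount. The figure of about 60 to 64 h is a maximum. It rests on assumed weekday services of 8 to 12 h, no recording continuing over the weekend, no routine EEG and no clinical sign of recovery. The number of restricted centres is not given, so the share of episodes affected cannot be stated.

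Separately, an ictal EEG listed by date alone cannot be ordered against a same-day drug outside the subgroup diagnosed by response to an intravenous ASM. This bears directly on the question about EEG patterns in NCSE, and it is the part that analysis cannot repair afterwards.

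**What to change.** 1. Record the date and time of the ictal EEG. Use its pattern as a predictor only when it precedes the drug or treatment line under study. If the data-capture form already holds the time, correct Table 1 to say so.
2. For EEG-defined SE, record the last time SE was confirmed present and the first time it was confirmed absent. Analyse duration as interval-censored, or at least add a sensitivity analysis restricted to patients under cEEG at cessation.
3. Limit the claim in the Study design section to patients under cEEG at the time of cessation.

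The cost is two or three extra timestamps per episode and slightly wider intervals for NCSE duration, which would reflect what was actually observed.

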### Objectives

The main objectives of the study are to assess patient characteristics, treatment modalities, to analyze and collect EEG features and outcome of adults treated for SE and identify predictors of outcome. Data assessed in this study could also identify gaps and opportunities of the management of this medical emergency.

More specifically, the following questions will be addressed:

Which factors determine global outcome at the time of hospital discharge?Which factors are associated with refractoriness and super-refractoriness?What are the efficacy and safety issues associated with each treatment?What are the characteristics of EEG in NCSE and do they carry clinically relevant information?How could we better classify SE taking semiology, etiology, and EEG into account?Are there differences in the pattern of care and outcome between the centers?

